#### Secondary outcome measures

2.6.2

The Olerud and Molander Ankle Score (OMAS) is a widely used validated patient questionnaire for ankle injuries which scores pain, stiffness, swelling, and various functional abilities from 0 to 100 with 0 representing total impairment, and 100 representing a perfect ankle. The OMAS has high reliability, and high structural validity for assessment of ankle injuries [23]. Minimal Clinical Importance Difference (MCID) is the smallest difference in a patient reported outcome measure that a patient can consider beneficial. The MCID for patients with ankle injuries who underwent ORIF was reported to range between 10.5 and 15.0 points (median 12.5) at three to six months follow-ups [24].

Other secondary outcomes will include a health quality of life survey using SF-36 health survey, and the Self-Reported Foot and Ankle Score (SEFAS). SEFAS is foot and ankle specific Patient Reported Outcome Measure (PROM) scored from 0 to 48, with a higher score indicating a more favourable outcome. It was identified with high content validity and high internal reliability (ICC = 0.93) with no ceiling and floor effect [25]. Time to return to work, time to full weight bearing without walking aids, and return to pre-injury activities will be obtained from patients’ logs in their periodic visits.

Possible post-operative complications will include total and individual complications including venous thromboembolism, wound complications (superficial, and deep wound infection, and wound dehiscence), loss of reduction, fracture malunion/mal-reduction, non-union and implant failure requiring revision surgery. Total complications will be calculated as the ratio of participant with any type of complications to all participants at 6 months post-surgery. Evidence of venous thromboembolism or wound complication will be documented as yes/no during hospitalisation and up to six weeks post-surgery from the patient's medical record. Superficial infection will be as defined by the National Library of Medicine, where infection is confined to the skin and subcutaneous tissues of the incision. Deep wound infection involves infection in the muscles and facial layers [26,27] requiring surgical debridement. Dehiscence of the wound will also be recorded and categorized as a deep wound complication.

At six weeks, three and - six months post-surgery, x-rays will be assessed by the orthopaedic team for fixation-related complications including reduction loss, malreduction/malunion, implant failures and non-union. Reduction loss will be defined as a displacement ≥ 2 mm compared with intraoperative images, or syndesmosis widening. Implant failure will be a breakage of the plate or screws. Non-union will be defined the absence of radiologic or clinical evidence of healing at six months post operation as determined by the orthopaedic team [28,29]. These will be collected from surgeon's x-ray interpretation during patients' clinic visits.

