### Eligibility criteria

2.3

Patients who are treated with open reduction internal fixation due to a unilateral ankle fractures will be sought for study enrolment. Stable fixation must be achieved by the operating surgeon. While subjective, this is likely to include criteria such as the patient having good quality bone, a good lag screw, and no significant unexpected comminution. Inclusion criteria will be skeletally mature patients (closed distal tibial physes) who are operated on due to closed ankle fractures. There is no upper age limit for inclusion. Fracture patterns will include isolated medial, lateral or posterior malleolus fractures, bimalleolar and trimalleolar fractures. Additionally, ankle fractures treated with an external fixator prior to definitive surgery will be included. These criteria were selected as no study has yet shown the association between the type of fractures and post-surgical outcomes (e.g., Quality of Life, Function scores, complications) [[19], [20], [21]], thus, if the other inclusion criteria are met, patients with different types of fracture will be included. Patients must be physically active (with or without walking aids) in the community before the injury and must speak English or have an interpreter available.

Exclusion criteria will include fractures where stability is still questionable following fixation, as deemed by the operating surgeon. Patients with active infection at the surgical site, any compound fracture, pathological fractures, Pilon fractures, or concurrent injuries that preclude adhering to the follow up protocol will be excluded. We will exclude participants who are unable to follow the protocol due to neurologic disorders (i.e., cognitive impairment, substance abuse, mental illness, intellectual disability, and dense peripheral neuropathy) or significant additional physical impairment (i.e. polytrauma patients with other limb, head or visceral injuries). Any fracture where syndesmosis stabilisation is required will be excluded as post-rehabilitation practices are more conservative with this type of fracture [22]. We will exclude patients whose follow up care will be provided outside of Christchurch Hospital.

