### Data collection

2.5

Patient baseline characteristics and hospital data will be collected through electronic medical records during hospitalisation and at discharge by research team members. The data will consist of participants demographics including age, sex, weight, height, BMI, ethnicity, pre-injury level of activity, smoking status, medical comorbidities, and employment status, injury characteristics including date of injury, mechanism of injury, and fracture classification, and treatment details including the date of surgery, type of fixation, and hospital length of stays. We will also record these data from patients who were excluded due to the surgeon deeming fixation unsuitable for immediate weight bearing. This will allow us to further identify if any particular demographic is disproportionately excluded, and minimise the risk of bias in our sample selection for both this pilot, and the full RCT. This will enhance the inclusion and patient selection process in the full RCT.

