#### Follow-up time points

2.6.3

Patient reported outcomes and radiographs will be obtained at six weeks, three and six-months post-surgery. Complications reported by the orthopaedic team will be documented by the research assistants from patient's medical records. The study timeline for participants recruitment and follow-up visits is described in Table 1 and Fig. 1.

**Table 1 tbl1:** Study timeline.

Assessment	Preoperative	Postoperative	2 weeks	6 weeks	3 months	6 months
**X-ray**	x			x	x	x
**CT-scan**	x					
**Participants screening**	x					
**Informed consent**	x					
**Participants eligibility**		x				
**Allocation**		x				
**Medical history**	x	x				
**Clinic visits (Complication outcomes)**			x	x	x	x
**Research visits (Functional outcomes)**				x	x	x

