### Sample size

2.10

The minimum clinically important difference for the OMAS was reported 10.5 at three months [24]. Considering the average standard deviation at 16 from prior studies, this gives a sample size of 50 per group for the main trial to achieve 90 % power at a two-sided alpha of 0.05. Given a 20 % drop-out, we will need 120 participants in total for the full trial. In order to minimise the sample size of the pilot and main trial combined, and considering the medium effect size of 0.66, it is recommended that 13 participants per group are recruited for the pilot study [31]. Given a drop-out rate of 20 %, we will need a total of 32 participants for the pilot trial. It is anticipated that these patients will carry over to participate in the ongoing full RCT, pending a successful pilot RCT, ethics approval and appropriate funding.

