## Statistical analysis

3

Descriptive statistics will be used to report participants’ recruitment rate per month, proportion of participants enrolled from the total number screened, adherence rate and the drop-out rate. Specific criteria to determine the feasibility of this study will be a recruitment of two participants per month, the adherence rate of 85 %, and the drop-out rate of ≤20 %.

SPSS (version 28.0; IBM Corporation, Armonk, NY) will be used for statistical analysis. We will report mean and SD for continuous data (OMAS, SEFAS, SF-36, time to full weight bearing, time to return to work and pre-injury activities) and percentage or number for categorical data (total and individual complications).

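### Walking-aid users are eligible, but one secondary outcome requires full weight bearing without an aid, so some fully recovered participants have no event time

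*Protocol article*

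**What the plan says.** Protocol article, section 2.3 (Eligibility criteria): "Patients must be physically active (with or without walking aids) in the community before the injury". The same section states: "There is no upper age limit for inclusion".

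Section 2.6.2 (Secondary outcome measures) lists the outcome and its source: "time to full weight bearing without walking aids, and return to pre-injury activities will be obtained from patients’ logs in their periodic visits". It makes no allowance for an aid used before the injury. The neighbouring outcome in that sentence, return to pre-injury activities, is relative to each participant's own starting point.

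Section 2.5 (Data collection) lists baseline items that include "pre-injury level of activity, smoking status, medical comorbidities, and employment status". Walking-aid use is not named.

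Section 3 (Statistical analysis) treats the time as an ordinary continuous variable: "We will report mean and SD for continuous data (OMAS, SEFAS, SF-36, time to full weight bearing, time to return to work". Follow-up ends at six months (section 2.6.3): "Patient reported outcomes and radiographs will be obtained at six weeks, three and six-months post-surgery".

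**The concern.** The eligibility rule and the outcome definition describe different populations. Section 2.3 deliberately enrols people whose normal walking may involve an aid. The event in section 2.6.2 fits only people whose normal walking does not. For a regular aid user, complete recovery and reaching the event are different things, and longer follow-up does not bring them together.

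Two things are at stake. First, the outcome mixes recovery with mobility before the injury, so an arm summary depends partly on who was allocated to that arm. Second, the problem may not be repairable afterwards. If the log captures only the date of walking unaided, the date on which an aid user returned to the usual aid is never recorded. If aid use is not recorded at baseline, the affected participants may not be identifiable either.

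**Working it through.** This is a check of one definition against another. The article gives no figure for this outcome.

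**1. The plan's own figure, to confirm that it is not involved.** The only powered calculation is the OMAS one in section 2.10, where "The minimum clinically important difference for the OMAS was reported 10.5 at three months". Inputs from that section: difference 10.5, SD 16, two-sided alpha 0.05, power 90%.
- Formula: n per group = 2 × (1.960 + 1.282)² × SD² / difference².
- Result: 2 × 10.51 × 256 / 110.25 = 48.8, so 49 by the normal approximation. The t-test version gives 49.8, so 50.
- The stated 50 per group reproduces. It does not use the walking-aid outcome, so redefining that outcome leaves it unchanged.

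**2. The definitions side by side.**

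| Participant before injury | Eligible under 2.3 | State at full recovery | Event under 2.6.2 |
|---|---|---|---|
| No aid | Yes | Full weight bearing, no aid | Reached |
| Occasional aid | Yes | Full weight bearing, aid at times | May be reached |
| Regular aid | Yes | Full weight bearing with the usual aid | Not reached at any visit |

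The third row is the problem. It does not depend on the arm or on the length of follow-up.

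**3. What a mean and SD can do with the third row.** Each participant needs a number. One with no event date has none, so the summary either leaves that person out and describes only those who came to walk unaided, or uses a value that was not observed. In an arm of 32/2 = 16, one person is 1/16 = 6.25% of the arm.

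**4. How many might be affected.** The article does not give the share q of pre-injury aid users. The values below are assumptions, for illustration only. With N = 32, the expected number is 32q and the chance of at least one is 1 − (1 − q)^32.

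| Assumed q | Expected number of 32 | Chance of at least one |
|---|---|---|
| 3% | 1.0 | 62% |
| 5% | 1.6 | 81% |
| 10% | 3.2 | 97% |
| 20% | 6.4 | 99.9% |

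These are counts of aid users. The number with no event is smaller if some used an aid only occasionally.

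**The case against.** The strongest reply is that this is a condensed article, and that handling of participants who do not reach an event usually sits in the full protocol or the SAP. That is right about handling. No criticism is made here of a missing censoring or imputation rule. It does not answer the point about the definition, because an analysis plan cannot supply a date that was never logged.

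A second reply is that the impact is small: a secondary outcome, reported descriptively, in a pilot whose success criteria are recruitment, adherence and drop-out. This stands. It is also fair that return to pre-injury activities, already listed, captures some of the recovery of aid users.

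Several stronger readings are tempting but not supported.
- A reader might infer that aid users will be scored as failures. The article states no handling at all, and a mean and SD point to omission or imputation.
- A reader might infer that every admitted aid user can never reach the event. Section 2.3 also covers occasional use, and such a person could reach it. The point holds for those who regularly needed the aid.
- A reader might try to state the bias in weeks. That needs an imputed value and a typical recovery time, neither of which the article gives, and the shift so calculated would not arise if such participants were simply omitted.
- A reader might extend the point to time to return to work, because retired people are eligible. The article does not say that outcome covers the whole sample, and section 2.5 collects "smoking status, medical comorbidities, and employment status", so it can be restricted to those who had work.

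**Conclusion.** The mismatch between sections 2.3 and 2.6.2 is real and lies in the stated text. A participant who regularly used an aid and recovers fully to that state has no event time, and the summary planned in section 3 cannot represent that person without omission or imputation.

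The effect on the pilot is limited. The number affected is unknown, and the range of about 1 to 6 of 32 rests wholly on an assumed share of 3% to 20%. The feasibility conclusions and the 50 per group do not change.

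It is still worth correcting now. Section 2.10 anticipates that pilot participants will carry over to the full RCT, subject to a successful pilot, ethics approval and funding, and section 5 presents the pilot as the place to refine the design. An event definition that misses part of the enrolled population would pass into the main trial with these participants' data.

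**What to change.** - **Section 2.6.2:** define the event as full weight bearing with no more walking aid than the participant used before the injury.
- **Section 2.5:** add pre-injury walking aid (none, stick, crutches, frame) to the baseline data. Because the trial is open label, record it before allocation is known; consent before surgery gives the occasion.
- **Patient log:** carry the pre-injury aid on the log and record the date on which the participant is back to that level.

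For participants who used no aid before the injury, the new event is the same as the present one, so their aid-free date can still be reported and compared with other studies.

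The cost is one new baseline field. The eligibility rule accepts patients with or without an aid, so it can be applied without recording which, and this item is an addition. There is also a slight loss of comparability with studies that use an aid-free definition for everyone. Eligibility, treatment and sample size do not change.

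### The 6-month total complication rate includes thromboembolic and wound events that are documented only to week 6, and implant failure is worded in two ways that give different counts

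*Protocol article*

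**What the plan says.** Section 2.6.2 (Secondary outcome measures) lists the complications as "total and individual complications including venous thromboembolism, wound complications (superficial, and deep wound infection, and wound dehiscence", followed by "loss of reduction, fracture malunion/mal-reduction, non-union and implant failure requiring revision surgery". The summary measure is then set: "Total complications will be calculated as the ratio of participant with any type of complications to all participants at 6 months post-surgery". The next sentence fixes how VTE and wound events are captured: they "will be documented as yes/no during hospitalisation and up to six weeks post-surgery", from the medical record.

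The following paragraph of the same section has x-rays read for fixation-related complications at six weeks, three months and six months. There the definition reads: "Implant failure will be a breakage of the plate or screws". It carries no revision condition.

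Table 1 (section 2.6.3) has a row "Clinic visits (Complication outcomes" marked at 2 weeks, 6 weeks, 3 months and 6 months. The text of section 2.6.3 adds that complications reported by the orthopaedic team will be taken from medical records, and it sets no week-6 limit.

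Section 2.4 keeps the delayed weight bearing (DWB) arm off the ankle for six weeks, while the immediate (IWB) arm may load it within 24 hours. Section 2.8 places randomisation after the operation is complete.

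**The concern.** The total has a 6-month horizon, but two of its named components have a 6-week one. Under the stated rule, a wound dehiscence or deep infection in month 3 is a complication within 6 months that is not documented for the total. The cut-off also falls where the intervention contrast changes. In the IWB arm the window covers about six weeks of permitted loading. In the DWB arm it covers none, so wound events in that arm's loading phase lie outside it.

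The implant-failure wording is a separate problem in the same composite. A broken screw left in place is counted under one sentence and not under the other.

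The Aim in the Introduction makes the absence of an increase in complications part of the question for the follow-on trial, and section 2.10 anticipates that pilot patients will carry over into it. A truncated or ambiguous complication count in the pilot could therefore pass into the definitive dataset.

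**Working it through.** The plan states no complication figure to reproduce, so the check is a comparison of the passages, with simple arithmetic to show scale.

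**1. Horizon against capture window**

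- Horizon of the total: 6 months, about 26 weeks (section 2.6.2).
- Capture of VTE and wound events: surgery to week 6 (section 2.6.2).
- Share covered: 6/26 = 23%. Share not covered: 20/26 = 77%.
- Complication visits after week 6: two, at 3 and 6 months (Table 1).

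The 23% is a share of calendar time, not of events. Many such events may occur early, and the documents do not say how many.

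**2. What one participant is worth**

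With 32 participants at 1:1 (sections 2.8 and 2.10), one participant reclassified moves the overall rate by 1/32 = 3.1 percentage points, or one arm's rate by 1/16 = 6.25 points. This holds for any event in a trial of this size. It shows sensitivity and does not measure an error.

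**3. Possible number missed (assumed inputs)**

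Let p be the 6-month risk of a VTE or wound event, and s the share of those events that fall after week 6. Both are assumptions. The expected number missed is 32 × p × s, and the chance of missing at least one is 1 − (1 − p × s)^32.

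- p = 5%, s = 10%: 32 × 0.005 = 0.16 events; chance 15%.
- p = 10%, s = 25%: 32 × 0.025 = 0.8 events; chance 56%.
- p = 15%, s = 50%: 32 × 0.075 = 2.4 events; chance 92%.

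The range is wide because nothing in the documents narrows it.

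**4. Implant failure, case by case**

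The list in section 2.6.2 has "non-union and implant failure requiring revision surgery"; the x-ray paragraph has "Implant failure will be a breakage of the plate or screws".

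- Breakage with revision: counted under both.
- Breakage left in place: counted under the x-ray paragraph only.
- Failure without breakage that needs revision: not counted under the x-ray paragraph; counted under the list if failure there is meant more broadly than breakage.

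The two wordings do not give the same count, and the text does not say which one enters the total.

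**5. Malreduction (conditional)**

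The term appears only paired with malunion, as in "loss of reduction, fracture malunion/mal-reduction", and is not defined. If it means the position left at surgery, it precedes randomisation and cannot be an effect of allocation. To see what that would do, assume arm rates of 10% and 20% without it, and add an independent malreduction risk m to both through q = 1 − (1 − p)(1 − m).

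- m = 0: 10.0% and 20.0%; risk difference 10.0 points; risk ratio 2.00.
- m = 5%: 14.5% and 24.0%; risk difference 9.5 points; risk ratio 1.66.
- m = 10%: 19.0% and 28.0%; risk difference 9.0 points; risk ratio 1.47.

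On that meaning the contrast is diluted, not systematically shifted. If the term is a synonym for malunion, the question does not arise.

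**The case against.** Three stronger readings are tempting, and the documents do not support them.

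- *The window is asymmetric between the arms, so the comparison is biased against IWB.* Time zero, duration and source are identical in both arms. Weeks 0 to 6 are also the period in which the allocated strategies differ, so a 6-week VTE and wound count is a legitimate outcome in its own right. What stands is narrower: the DWB arm's loading phase is outside the window. The loading argument concerns wound events; the documents give no reason to tie late VTE to loading.
- *Late events in the DWB arm can never be counted.* Table 1 and the text of section 2.6.3 provide for complication visits and record review without a week-6 limit, so some late events may be picked up. The passages are in tension, and the explicit rule for these two components is the one that stops at week 6.
- *The total counts malreduction that was fixed before randomisation.* The article does not say so. The term is paired with malunion, sits under post-operative complications and is read on x-rays from six weeks, which fits a single outcome of healing in a poor position. A missing definition in a condensed article is not itself a fault.

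On implant failure, the two sentences can be reconciled by taking the list as the subset of breakages that need revision. That is plausible, but the article does not say it.

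It is also fair that the pilot's primary outcomes are recruitment, adherence and drop-out, that the feasibility criteria in section 3 use only these, and that complications are reported as numbers or percentages. This limits the importance of the point but does not remove the mismatch.

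**Conclusion.** Two points hold on the text alone. A total defined at 6 months includes two components whose stated documentation ends at week 6, so following the rule leaves out any later VTE or wound event. Implant failure has two wordings that give different counts, with no statement of which applies to the total.

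The uncovered period is about 20 of 26 weeks, but the number of events lost cannot be derived; the 0.16 to 2.4 events above rest wholly on assumed risks. Neither conclusion needs an assumption about event frequency, a bias between arms or a particular meaning of malreduction.

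Importance is modest. This is a secondary outcome, reported descriptively in a 32-patient feasibility pilot. It is worth correcting because the same patients and definitions may pass into a trial that asks whether complications increase.

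**What to change.** - Document VTE and wound complications in both arms through 6 months, from the visits in Table 1 and the medical record, and report the 6-week count separately. Failing that, label them a 6-week outcome and keep them outside the 6-month total.
- Reconcile the two implant-failure sentences by stating which version enters the total, and record hardware breakage and revision surgery as separate items so that either count can be recovered.
- Say what malreduction means. If it is the position left at surgery, report it separately from the post-randomisation total. If it is a synonym for malunion, only the wording needs tidying.

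The cost is a few sentences of outcome wording and continued record review to 6 months. No visit or procedure is added, and patient care does not change.
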